### Safety assessments

Inositol and folic acid are considered supplements and are not expected to be associated with adverse events when administered at the normal daily dosage. However, participants will be asked to report all potential adverse events (AEs) at each visit point, and all AEs reports will be recorded and assessed by the investigators. In the case of unexpected serious adverse effect, the participant will be hospitalized or treated at the high-risk pregnancy department of our hospital at no charge.

A data monitoring committee will not be formed as myo-inositol is a natural product that is daily consumed in various compounds such as fruits and grains. Furthermore, previous trials that evaluated inositol in pregnancy have not reported adverse effects. Nevertheless, an interim analysis will be performed following the recruitment of the first 40 patients to assess for potential unexpected adverse effects that will be considered as a reason to discontinue the trial.

### Sample size calculation

Given the lack of previous data in this field, we sought to determine the sample size of our study based on two types of calculations. The largest sample size was finally used to ensure that our study would not be underpowered. The level of statistical significance was set at 0.05 and the power of the study at 0.80 using an 1/1 allocation. In our first attempt, we used the study of Genazzani et al. [10] and calculated the sample size taking into account the fasting insulin levels. The effect size was calculated to be 0.86 and the sample size in each group of 30 women. In the second attempt, we used the decline in the prevalence of GDM that was observed in the study of D’Anna et al. [20] (14 vs. 33.6%). According to the latter sample size calculation, 73 women were needed in each group. With an estimated 10% of patient withdrawal and lost to follow up rates, the final number of enrolled women was estimated to 160 women. Given the relevance of the prevalence of GDM in the latter study to that of the Greek population that is treated in our hospital [23] and other studies in this field that supports an almost 50% reduction in GDM following inositol treatment [16, 24], we chose to include the latter calculation in our study. The G power tool v. 3.1.9.2 was used in all cases.

### Data management and quality control

The main study will be preceded by a 4-month pilot study to assess the compliance of participants in the study group related to the consumption of myo-inositol and their compliance regarding the re-evaluation of glucose levels at 19–20 and 26–28 weeks.

All data will be tabulated in preconstructed tables using the Microsoft Access software, which ensures the homogeneity of data entry. All electronic data will be double-checked from two independent researchers to preclude the possibility of misreporting. Only predefined variables will be enlisted. Interim evaluation of the process of data handling will be provided following the recruitment of the first 40 patients to audit patient adherence as well as the data acquisition process. The access to the study’s dataset (for both interim evaluation and final analysis) will be granted only to the statistician that will be involved in the study. Physicians will not be able to access this dataset prior to the publication of this study.

### Statistical analysis

All analyses will be performed in the intention to treat (ITT) population of our study. Sensitivity (per-protocol analysis) will be also provided taking in mind parameters that may deviate from planned treatment such as failure to adhere to the recommended dosage, drug dose change requested by the primary physician or the patient in response to adverse effects, and concurrent consumption of insulin. The normality of the distribution of our findings will be assessed with the Kolmogorov-Smirnov test and graphical methods. Parametric and non-parametric tests will be used based on these latter findings accordingly. The chi-square test will be used to compare discrete variables and Fisher’s exact test will be used to compare discrete variables with less than 5 observations (if any). Adjusted analysis will be performed as well taking into account the variables of age and body mass index. Logistic regression will be performed in an attempt to identify the impact of myo-inositol in a multivariate model analysis (sensitivity analysis). Complete case analysis will be performed and multiple imputation will not be attempted. Exploratory subgroup analyses will be performed for subsets of patients with risk factors (obesity, history of GDM, family history of diabetes, PCOS) if an arbitrary cut-off of at least 20 patients per group (myoinositol – control) will be reached. All analyses will be performed with the SPSS 21.0 package (IBM Corp. Released 2012. IBM SPSS Statistics for Windows, Version 21.0. Armonk, NY: IBM Corp.).

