Inositol phosphoglycan is an intracellular insulin mediator, which is associated with insulin sensitivity in conditions of insulin resistance, such as T2D [12, 13]. Gestational diabetes mellitus is characterized by increased urinary excretion of inositol phosphoglycan, which shows a positive correlation with blood glucose levels [14, 15]. This observation has also been reported in patients with insulin resistance related to PCOS [16], who have been successfully treated with myo-inositol and folic acid [17]. In a previous study, D’Anna et al. suggested that myo-inositol may actually prevent the occurrence of GDM in PCOS women [18]. The insulin resistance of the syndrome seems to be characterized by a defect in tissue availability or utilization of inositol mediator; therefore, the supplementation of that mediator would improve the intracellular effect of insulin [13, 14, 16, 17]. These findings support the hypothesis that inositol administration could decrease insulin resistance related to GDM. Inositol is considered as a dietary supplement rather than a drug and is present in many foods, such as cereals, corn, legumes, and meat. It is synthesized principally by the liver. To date, a handful of randomized trials have assessed the impact of inositol regimens on the incidence of GDM. Of those, two studies that recruited overweight pregnant women observed > 50% reduction in the incidence of GDM [17, 19], and one study that included obese women observed nearly 60% reduction [20]. Women with polycystic ovarian syndrome may also benefit from inositol supplementation during pregnancy as the incidence of GDM seems to be reduced by more than 60% according to the findings of another study [18]. Results, however, seem to be conflicting in cases with a family history of GDM as D’Anna et al. observed a significant effect [13] whereas Farren et al. did not [21].

This randomized, open-label study is designed to evaluate the impact of myo-inositol supplementation from the first trimester of pregnancy on GDM prevalence. Results of this study will provide evidence regarding the value of myo-inositol as a safe intervention for the prevention of GDM.

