### Aims

We hypothesize that myo-inositol supplementation from 11 to 13^+6^ weeks of gestation until the time of GDM diagnosis (26–28 weeks of gestation) will reduce the incidence of GDM. To test this hypothesis, we will compare an intervention group and a control group. The intervention group will receive myo-inositol and folic acid, while the control group will receive folic acid alone.

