### Design and setting

This is a single-center, open-label, randomized controlled trial, which will be conducted in the First Department of Obstetrics and Gynecology in cooperation with the Diabetes Centre of First Department of Endocrinology in Alexandra Hospital in Athens, Greece. The study aims to enroll 160 healthy pregnant women over a 2-year period. Participants will be randomized, using a 1:1 ratio, to receive either myo-inositol and folic acid (4000 mg myo-inositol and 400 mcg folic acid daily) or folic acid alone (400 mcg folic acid daily). At 11–13^+6^ weeks of gestation and after providing written informed consent, patients will be randomly allocated in two groups until 26–28 weeks of gestation. At the time of study entry, Diabetes Centre of Alexandra Hospital will offer measurements of fasting blood glucose and glycated hemoglobin to all participants of both groups. At 19–20 weeks of gestation, the same measurements will be repeated to all participants. Finally, at 26–28 weeks of gestation, the 2 h 75 g oral glucose tolerance test (OGTT) will be offered for the diagnosis of gestational diabetes [4, 22]. The overall flow of the trial is shown in Fig. 1.

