### Participants

Healthy adult pregnant women with singleton pregnancy at 11–13^+6^ weeks of gestation will be held eligible for inclusion in the present study.

Research assistants will discuss the expected outcomes and the potential adverse effects of myo-inositol in Greek or English language. Participants will be given a consent form and separate information sheets including information on the main aspects of the trial. Research assistants will obtain the signed consent form from patients willing to participate in the trial.

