### Inclusion criteria

Patients will be enrolled if they are aged over 18 years old without pre-existing impaired glucose tolerance, have singleton pregnancy, and provide signed informed consent.

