### Exclusion criteria

Age under 18 yearsMultiple pregnanciesPre-existing diabetes mellitusConsumption of steroidsHypertensive disordersHypothyroidismPre-existing renal or hepatic impairmentBeta thalassemia carriersVaginal bleeding (e.g., placental abruption)Special diets (e.g., lactose intolerance)Inadequate monitoring during pregnancy

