In a retrospective study conducted in pregnant women affected by PCOS, D’Anna et al. [18] observed that myo-inositol administration, throughout the pregnancy course, may reduce the prevalence of GDM. In particular, these authors demonstrated a lower prevalence of GDM in PCOS women who achieved conception on myo-inositol supplement and continued this regimen during pregnancy, compared with PCOS women who conceived on metformin and discontinued it after the diagnosis of pregnancy (17.4 vs. 54%, *P* = 0,001).

Another open-label RCT [13] reported a significant decrease of GDM incidence in non-obese women, with a family history of T2D, treated with myo-inositol and folic acid from the end of the first trimester throughout the remainder of the pregnancy compared with similar control subjects treated with folic acid alone (6 vs. 15.3%, *P* = 0.04). Moreover, fetal macrosomia was significantly reduced (0 vs. 7%, *P* = 0.007) in the myo-inositol group and the mean birth weight was also significantly reduced in the treatment group (*P* = 0.018). The authors also reported a statistically significant decrease of fasting plasma glucose (*P* = 0.001) and 1-h plasma glucose on the 75 g oral glucose tolerance test (OGTT) (*P* = 0.02) in the myo-inositol group compared to the control group. The same authors [20] reported a lower incidence of GDM (14 vs. 33.6%, *P* = 0.001) and a greater reduction in the homeostasis model assessment of insulin resistance (− 1.0 ± 3.1 vs. 0.1 ± 1.8, *P* = 0.048) among 99 obese pregnant women treated with myo-inositol and folic acid from the first trimester to delivery compared to 107 obese pregnant women treated with folic acid alone.

Matarelli et al. [16] demonstrated that maternal/fetal/neonatal GDM in women at high risk was well controlled when treated with myo-inositol. In particular, women treated with myo-inositol showed a significantly lower prevalence of GDM in mid-pregnancy (risk ratio (RR) = 0.127, 95% CI [0.032–0.502], *P* = 0,001), required less insulin therapy (RR = 0.136, 95% CI [0.018–1.031], *P* = 0.053), delivered at a later gestational age (95% CI [− 2.578 to − 0.948], *P* = 0.001), and had significantly smaller babies (birth weight is expressed as percentiles, 95% CI [10.807–30.116], *P* = 0.001) with fewer episodes of neonatal hypoglycemia (RR = 0.052, 95% CI [0.003–0.849], *P* = 0.038) compared to placebo.

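### Women already taking myo-inositol are not excluded, and non-study inositol is neither named as a deviation nor visible to the tablet count, so control-arm use could dilute the contrast unnoticed

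*Protocol article*

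**What the plan says.** All references are to the Protocol article.

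- **Aims.** The intervention group receives myo-inositol with folic acid, "while the control group will receive folic acid alone".
- **Design and setting.** "This is a single-center, open-label, randomized controlled trial".
- **Inclusion criteria.** "Patients will be enrolled if they are aged over 18 years old without pre-existing impaired glucose tolerance"; the remaining conditions are singleton pregnancy and signed consent.
- **Exclusion criteria.** There are eleven items. They reach one concomitant medication (steroids) and diet ("Special diets (e.g., lactose intolerance"), but none concerns inositol.
- **Background.** "Inositol is considered as a dietary supplement rather than a drug".
- **Participants.** Before consent, "Research assistants will discuss the expected outcomes and the potential adverse effects of myo-inositol".
- **Discussion.** A cited retrospective study is described as including "PCOS women who achieved conception on myo-inositol supplement and continued this regimen during pregnancy".
- **Interventions.** Adherence is judged at each visit from the study tablets left in the returned bottles.
- **Data management and quality control.** The pilot looks at myo-inositol compliance in the study group. Only predefined variables are entered, and the article does not list them.
- **Statistical analysis.** Intention to treat is the analysis population. The per-protocol sensitivity analysis considers departures from planned treatment, introduced as examples: "failure to adhere to the recommended dosage, drug dose change requested by the primary physician or the patient in response to adverse effects", and concurrent insulin. PCOS is one of the exploratory subgroups, to be analysed if each arm has at least 20 such women.

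**The concern.** The treatment contrast is interpretable only if control women are largely unexposed to myo-inositol. The eligibility list covers steroids and diet but not the test agent, so a current user can enter and be assigned to control.

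Several features make this plausible in this trial. The agent is a supplement rather than a drug. Allocation is known, and every candidate has heard about myo-inositol before consenting. Women with PCOS can enrol, and the article itself describes such women conceiving on myo-inositol and continuing it.

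The Randomization and blinding section defends open-label treatment on the ground that the OGTT is biochemical. That argument covers outcome assessment. It does not cover what control women take.

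The stake is a diluted primary comparison. A null or weak result could not be told apart from control-arm exposure, and if use is concentrated in women with PCOS, that subgroup would be hit hardest. The described checks would not necessarily show it, because a count of study tablets says nothing about other products.

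**Working it through.** **Inputs.** From Sample size calculation: GDM 33.6% in control and 14% on myo-inositol, alpha 0.05, power 0.80, 1:1 allocation, 73 per group, 160 enrolled (80 per arm) after a 10% allowance for withdrawal and loss. Sidedness is not stated; two-sided is used here because it reproduces the plan's figure. *Assumptions, not in the document:* a fraction c of control women take non-study inositol, and each takes on the intervention-arm risk.

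**Step 1: reproduce the stated figure.** With p̄ the mean of the two rates, A = √[2p̄(1−p̄)] and B = √[p₁(1−p₁) + p₂(1−p₂)],

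n = (1.960·A + 0.8416·B)² / (p₁−p₂)².

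Here p̄ = 0.238, A = 0.6023, B = 0.5861 and p₁−p₂ = 0.196, so n = (1.1805 + 0.4933)² / 0.0384 = 72.9, or 73 per group. This agrees with the plan. The only allowance added to it is for withdrawal and loss; there is none for control-arm exposure.

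**Step 2: diluted control rate.** p₁(c) = 0.336 − c × (0.336 − 0.14) = 0.336 − 0.196c.

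**Step 3: power.** Power = Φ{[(p₁−p₂)√n − 1.960·A] / B}, with A and B recomputed at p₁(c).

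Worked case, c = 0.10 and n = 73: p₁ = 0.3164, difference 0.1764, p̄ = 0.2282, A = 0.5935, B = 0.5803. Then (0.1764 × 8.544 − 1.960 × 0.5935) / 0.5803 = (1.507 − 1.163) / 0.5803 = 0.593, and Φ(0.593) = 0.723.

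| Exposed controls (c) | Of 80 controls | Control GDM rate | Difference (points) | Power, 73 per arm | Power, 80 per arm | n per arm for 80% |
|---|---|---|---|---|---|---|
| 0 | 0 | 33.6% | 19.6 | 80.0% | 83.6% | 73 |
| 5% | 4 | 32.6% | 18.6 | 76.4% | 80.1% | 80 |
| 10% | 8 | 31.6% | 17.6 | 72.3% | 76.3% | 88 |
| 20% | 16 | 29.7% | 15.7 | 63.3% | 67.3% | 108 |

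If exposed controls gained only part of the benefit, c would be multiplied by that part. For example, 20% exposed with half the benefit gives the 10% row.

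**Step 4: could the described analyses show it?** A control woman who takes inositol has departed from her planned treatment, so the open per-protocol list could include her. That requires her use to be recorded. The only exposure measure described is the count of study tablets, and she can return exactly the right number while taking a non-study product.

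**The case against.** The strongest reply has four parts.

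1. **The per-protocol list is open.** The examples are introduced as such, and planned treatment for controls is folic acid alone. A reader might infer that control-arm inositol is not a per-protocol deviation, or that the sensitivity analysis cannot reveal it. The text supports neither. It supports only that such use is not named and not described as recorded, so it may be missed. Nor does non-adherence remove only myo-inositol women: tablet counts apply to all participants.
2. **There is no evidence of use in this population.** The PCOS passage describes an outside retrospective study, and no exposure rate is given for this hospital. The 20% row means 16 of 80 controls. If PCOS were the main source, that would need many such women in the control arm, and the plan does not assume that even 20 per arm will be reached. This stands: the power figures are conditional, and exposure is a risk, not an established fact.
3. **The article condenses a fuller protocol.** Recording of concomitant supplements and a detailed per-protocol definition may sit there. That tempers the recording point. It does less for eligibility, because the criteria are printed as a complete list and the gap lies in that list.
4. **The bias is conservative.** Dilution costs power and shrinks the estimate; it does not create a false positive. This is correct, and it limits the seriousness.

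A reader might also extend the point to metformin. The Discussion does not support that: the women in the cited study who conceived on metformin stopped it once pregnancy was diagnosed.

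**Conclusion.** The concern holds in a limited form. As printed, the criteria allow a current myo-inositol user to be randomised to the folic-acid-only arm. Non-study inositol is not named among the deviation examples, and the tablet count would not detect it. Any control-arm use would move the intention-to-treat difference toward zero if myo-inositol is effective.

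The size is unknown because no rate is given. Under the full-benefit assumption, 5% to 20% exposure lowers power from 80% to between 76% and 63% with 73 evaluable per arm, or from about 84% to between 80% and 67% with 80. At 5% exposure with all 80 evaluable, the planned power is just kept; at 10% or more it is not. These are illustrations, not a prediction. The case for acting is that the change is cheap and affects who enters the comparison.

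**What to change.** - **Exclusion criteria:** for women still to be enrolled, add current use of any inositol-containing supplement.
- **Interventions:** at the existing visits, ask women in both arms about non-study inositol and record the answer as a predefined variable. Include the women already enrolled.
- **Statistical analysis:** name non-study inositol in either arm as a per-protocol deviation. Keep intention to treat as the primary analysis, unchanged.

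**Cost.** One exclusion line, one question per visit and one line in the per-protocol definition. A few women, mainly with PCOS, would become ineligible. Trial status reports 48 recruited against 42 planned for the first six months, so a small loss looks affordable. The criterion would change during recruitment: those 48 women, 30% of 160, can be asked about use but not excluded, so the report should say from which point the new criterion applied.

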### Interventions

As routine for the geographical area where this study is conducted, the control group will be given 400 mcg of folic acid orally per day, while the intervention group will be given 4000 mg of myo-inositol plus 400 mcg of folic acid per day (2000 mg myo-inositol and 200 mcg folic acid twice daily) from 11 to 13^+6^ weeks of gestation until 26–28 weeks of gestation. At the time of study entry, the Centre of Diabetes of Alexandra Hospital will offer measurements of fasting blood glucose and glycated hemoglobin to all participants of both groups. At 19–20 weeks of gestation, the same measurements will be repeated to all participants. Finally, at 26–28 weeks of gestation, the 2 h 75 g oral glucose tolerance test (OGTT) will be offered for the diagnosis of gestational diabetes [4, 22]. An evaluation of maternal glycemic status will be performed on monthly intervals until delivery and neonates will be followed up until 6 months of life.

Adherence will be monitored at every post-allocation visit by the responsible research physician. The participants must return the bottles at each visit and the physician will count the tablets left in the bottles. Participants with inadequate adherence will be recorded.

The oral combination of myo-inositol and folic acid and the oral tablet of folic acid alone are manufactured by Italfarmaco S.p.A (Milan, Italy).

A timeline of the study procedures is presented in Fig. 2.

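### Entry fasting glucose and HbA1c are offered to all women but left out of the named adjustment set (age and BMI), which loses efficiency: potentially material for those two outcomes, modest for GDM

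*Protocol article*

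**What the plan says.** - **Entry data.** Under Interventions (and again under Design and setting), the Diabetes Centre "will offer measurements of fasting blood glucose and glycated hemoglobin to all participants of both groups" at study entry, with the same measurements repeated at 19–20 weeks. Insulin is not listed among the entry measurements.
- **Outcomes.** Primary outcomes defines GDM by the 75 g OGTT at 26–28 weeks; a fasting value of 5.1 mmol/l or more is sufficient on its own. Secondary outcomes lists fasting glucose and HbA1c.
- **Binary outcomes.** Statistical analysis uses the chi-square test, or Fisher's exact test when counts are sparse.
- **Continuous outcomes.** "The normality of the distribution of our findings will be assessed with the Kolmogorov-Smirnov test and graphical methods", and the result decides between parametric and non-parametric tests. No covariate enters.
- **Adjustment.** "Adjusted analysis will be performed as well taking into account the variables of age and body mass index". A multivariable logistic regression is also listed, as a sensitivity analysis, with no covariates named.
- **Missing data.** Complete cases only, without multiple imputation.

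Nowhere are the entry glucose or HbA1c values used as covariates or to form a change from baseline.

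**The concern.** The baseline value of an outcome is usually among its strongest predictors. Here the baseline of two secondary outcomes, and of one component of the primary outcome, is planned for collection. The article does not leave the covariates open in its adjusted analysis: it names two and omits these. What is at stake is precision. Conditioning on a prognostic entry value narrows the interval for the treatment effect on fasting glucose and HbA1c, and to a lesser degree raises power for GDM, with no new measurement. The design is sized at its 80% target with almost no margin, so the precision is worth having.

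**Working it through.** **Inputs from the protocol article.** "The level of statistical significance was set at 0.05 and the power of the study at 0.80 using an 1/1 allocation"; GDM rates of 14% vs 33.6%; "According to the latter sample size calculation, 73 women were needed in each group"; 10% loss and 160 enrolled (Sample size calculation).

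**Inputs not in the documents (assumed).** Correlation of 0.2 to 0.6 between the entry value and the later value of fasting glucose or HbA1c. Odds ratio for GDM of 1.35 to 2.7 per SD of entry glycaemia. A combined age/BMI score with odds ratio about 1.5 per SD, correlated 0.3 with entry glycaemia.

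**Step 1: the plan's own figure.** Two-sided test, pooled variance, no continuity correction; mean rate (0.336 + 0.14)/2 = 0.238.

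n = [1.960 × √(2 × 0.238 × 0.762) + 0.8416 × √(0.336 × 0.664 + 0.14 × 0.86)]² / 0.196²
= (1.1804 + 0.4933)² / 0.038416 = 72.9, so **73 per group**. Power at 73 is 80.0%. The stated figure reproduces, and it rests on an unadjusted comparison.

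**Step 2: fasting glucose and HbA1c.** Take a difference that an unadjusted test detects with 80% power at 73 per group. ANCOVA on the entry value multiplies the residual variance by 1 − ρ², so

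power = Φ(2.8016/√(1 − ρ²) − 1.960), and equivalent total N = 146 × (1 − ρ²).

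For ρ = 0.3: 2.8016/0.9539 − 1.960 = 0.977, and Φ(0.977) = 0.836.

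| Assumed ρ | 1 − ρ² | Power | Equivalent total N (from 146) |
|---|---|---|---|
| 0.2 | 0.96 | 81.6% | 140 |
| 0.3 | 0.91 | 83.6% | 133 |
| 0.4 | 0.84 | 86.4% | 123 |
| 0.5 | 0.75 | 89.9% | 110 |
| 0.6 | 0.64 | 93.8% | 93 |

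**Step 3: GDM.** Simulation of 6,000 trials per row, 73 per group, marginal rates held at 33.6% and 14%; likelihood-ratio tests for the logistic models. Gains are in percentage points.

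| Assumed OR per SD | Chi-square | Age + BMI | Age + BMI + entry glycaemia | Gain over age + BMI | Gain over chi-square |
|---|---|---|---|---|---|
| 1.35 | 81.4% | 83.4% | 84.0% | 0.6 | 2.6 |
| 1.65 | 79.3% | 81.7% | 83.0% | 1.3 | 3.7 |
| 2.0 | 80.4% | 82.4% | 85.1% | 2.7 | 4.7 |
| 2.7 | 81.2% | 83.9% | 87.4% | 3.5 | 6.2 |

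The Monte Carlo standard error is about 0.5 point. Because the marginal rates are fixed, the true chi-square power is the same in every row and its spread is simulation noise; comparisons should be made within rows. Part of the last column is not due to entry glycaemia: an unadjusted likelihood-ratio test already gave 82.5%, 80.3%, 81.2% and 82.0%, about 0.8 to 1.1 points above chi-square, and age and BMI add more. The gain over age + BMI isolates the entry value.

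**Step 4: room in the logistic model.** 160 × 0.9 = 144, or 72 per arm. Expected GDM cases are 72 × (0.336 + 0.14) = 34.3. With arm, entry glucose, age and BMI (four slopes), that is 34.3/4 = 8.6 events per slope.

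**The case against.** The strongest reply is that nothing here is wrong. An unadjusted chi-square test in a randomised trial is valid, the sample size was built on it, and it reaches its stated 80% at 73 per group. That stands: the point concerns efficiency alone.

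The second reply is that the benefit for GDM is small. Age and BMI adjustment is already planned, the further gain is at most a few points, and every prognostic strength is assumed. Requiring women to be "without pre-existing impaired glucose tolerance" may also narrow the range of entry values and weaken their predictive strength. This stands too, and limits the claim for the primary outcome. It does not remove the case for ANCOVA on fasting glucose and HbA1c.

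Third, the article is a condensed account, and the sensitivity logistic regression leaves its covariates unnamed, so a fuller analysis plan could include entry glucose there. That is possible. But the article does name a set for its adjusted analysis, and entry glycaemia is not in it.

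Some stronger readings are tempting but not supported:

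- *That a chance imbalance in entry glucose would bias the result because randomisation is unstratified.* The article says only that the sequence is computer-generated; stratification is unstated, not ruled out. Chance imbalance is in any case covered by the test's type I error.
- *That the entry values exist for every woman and so adjustment is free.* They are offered, and some may be missing.
- *That women already at or above 5.1 mmol/l at entry seriously dilute the primary comparison.* The documents give no share of such women, the inclusion criterion may remove some, and the observed 14% and 33.6% may already contain them. Covariate adjustment would not remove such dilution anyway.
- *That the argument extends to HOMA-IR and the Matsuda Index.* No entry insulin is listed, so neither index has its own baseline.

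**Conclusion.** The point holds as a loss of efficiency. For fasting glucose and HbA1c the gain from ANCOVA can be material: 80% power becomes about 84% to 90% at assumed correlations of 0.3 to 0.5, equivalent to a 9% to 25% saving in women. For GDM it is modest: about 0.6 to 3.5 points beyond age and BMI for assumed odds ratios of 1.35 to 2.7 per SD. The gain over the planned chi-square test is 2.6 to 6.2 points, and it counts for the primary result only if the adjusted model is prespecified as the main analysis. The direction is secure whenever entry values are prognostic; the size depends on correlations and odds ratios that the documents do not give. A reader might infer that the trial is undersized or its primary test unsound because of this omission; the reproduced 73 per group shows otherwise.

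**What to change.** 1. Analyse fasting glucose and HbA1c by ANCOVA with arm, the entry value of the same measure, age and BMI, in place of the unadjusted test selected after the normality check.
2. Add entry fasting glucose to age and BMI in the prespecified adjusted logistic model for GDM, and state whether that model or the chi-square test is the main analysis. If chi-square stays as the main analysis, the adjusted result is supportive and the power for the primary test is unchanged.
3. State how women without an entry value are handled. Under the complete-case rule they would drop out of the adjusted models; a simple baseline imputation or a missing indicator keeps them.
4. Keep the GDM model to these few covariates, given about 34 expected events.

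The cost is wording in the analysis section, settled before the outcome data are examined by arm. No additional measurement, visit or participant is needed.

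### The subgroup plan looks only inside each risk-factor subset, from 20 women per arm, and states no comparison with women without the factor, so it cannot show whether the effect differs by risk factor.

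*Protocol article*

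**What the plan says.** Protocol article, Statistical analysis: "Exploratory subgroup analyses will be performed for subsets of patients with risk factors (obesity, history of GDM, family history of diabetes, PCOS") on the condition "if an arbitrary cut-off of at least 20 patients per group". The same section gives the general tests for discrete variables: chi-square, or Fisher's exact test when there are fewer than 5 observations. It also describes a logistic regression as a multivariate sensitivity analysis for the impact of myo-inositol, with adjustment for age and BMI named just before it. No arm-by-factor term is mentioned, and neither is an analysis of women without the factor.

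Protocol article, Sample size calculation: "The level of statistical significance was set at 0.05 and the power of the study at 0.80 using an 1/1 allocation"; at 14% vs 33.6%, "73 women were needed in each group". That calculation covers the overall comparison only.

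Protocol article, Background: earlier trials are reported as favourable in overweight, obese and PCOS women, but "Results, however, seem to be conflicting in cases with a family history of GDM".

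**The concern.** The unit of analysis is the subset that has the factor. A test or estimate there answers whether myo-inositol works in these women, with few of them to answer it. It does not answer whether it works better or worse than in the others, which is what a reader of a subgroup table wants to know. Near the 20-per-arm floor a non-significant result is the likely outcome even if every woman benefits equally, so one subset may reach p < 0.05 and the next miss it through sample size alone.

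At stake is how the secondary findings are read. The Background describes a literature whose results vary by risk group. A set of subset results with no comparison between women with and without each factor could look like more such variation when there is none. The primary result is not affected.

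**Working it through.** **Inputs.** From Sample size calculation: GDM rates 14% (myo-inositol) and 33.6% (control), alpha 0.05, power 0.80, 1:1 allocation. From Statistical analysis: floor of 20 per arm, four factors, chi-square or Fisher. From Discussion: 17.4% vs 54% in a retrospective study of women with PCOS. Sidedness is not stated; two-sided is assumed because it reproduces the stated sample size.

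**1. The plan's own figure.** With pooled rate p = (0.336 + 0.14)/2 = 0.238,

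n = [1.96·√(2·0.238·0.762) + 0.842·√(0.336·0.664 + 0.14·0.86)]² / 0.196² = [1.96·√0.3627 + 0.842·√0.3435]² / 0.0384 = 72.9, so 73 per arm. This matches the article.

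**2. Power inside a subset.** For n per arm, sum the product of the two binomial probabilities over all (n+1)² possible tables in which the two-sided p-value is below 0.05. The miss rate is 1 minus this sum.

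| Women per arm | Rates | Power, chi-square | Power, Fisher | Missed |
|---|---|---|---|---|
| 20 | 14% vs 33.6% | 31.1% | 20.6% | 69–79% |
| 30 | 14% vs 33.6% | 43.2% | 32.4% | 57–68% |
| 40 | 14% vs 33.6% | 55.1% | 45.7% | 45–54% |
| 20 | 17.4% vs 54% | 70.7% | 59.3% | 29–41% |

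At 20 per arm the expected number of GDM cases is 20·0.14 = 2.8 and 20·0.336 = 6.7. If the small-count rule is read as Fisher when any cell is below 5, it selects Fisher in about 88% of datasets and power is 20.7%. The upper end of the 69–79% range is then the realistic one at the floor.

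**3. Chance findings with no effect.** Take all four subsets at 20 per arm, tested independently. (Real subsets overlap, and to qualify a factor must be present in about 20/80 = 25% of each arm as enrolled.) Under the same reading of the rule, the error rate per test is 1.9% at a common GDM rate of 14%, 2.4% at 25% and 3.0% at 33.6%. Then 1 − (1 − 0.019)⁴ ≈ 7%, 1 − (1 − 0.024)⁴ ≈ 9% and 1 − (1 − 0.030)⁴ ≈ 11%. At the nominal 5%, which chi-square roughly keeps, it is 1 − 0.95⁴ = 18.5%.

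**4. What an interaction test would achieve.** Illustration: control rate 33.6% everywhere, the full planned effect inside the subset and none outside. The difference in log odds ratios is |ln(0.14/0.86) − ln(0.336/0.664)| = 1.134. Its variance is the sum of 1/[n·p(1−p)] over the four cells.

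- 20 per arm inside, 53 outside: SE 0.899, z = 1.26, power Φ(1.26 − 1.96) ≈ 24%.
- Even split (36 and 37 per arm): SE 0.773, z = 1.47, power Φ(1.47 − 1.96) ≈ 31%.

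**The case against.** The strongest reply is that the article gives subgroups one sentence, calls them exploratory, and calls the cut-off arbitrary. It names four factors in advance and sets a minimum size. It claims nothing about differences between subgroups, and its stated aim is overall GDM incidence. An interaction term is something an analysis plan, not shown here, could add.

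Much of this stands, and it limits the point. A reader might infer that the plan commits to significance tests inside each subset. The text does not say so; that follows only from the general sentence on chi-square and Fisher. A reader might also infer that 20 per arm is claimed to be adequate, but it is a floor below which nothing is analysed. Nor does the article set out to resolve the conflicting family-history results. The 69–79% miss rate belongs to the floor and the planning rates, and larger subsets or higher control rates lower it considerably.

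The reply does not remove the core. The article does fix a method: analysis of the subset with the factor. The exploratory label tempers what may be claimed, but it does not turn a within-subset result into a comparison of effects.

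**Conclusion.** The point holds as a modest improvement. As written, the subgroup analyses cannot show whether the effect of myo-inositol differs by risk factor. If they are judged by significance, a uniform benefit of the planned size would be missed 69–79% of the time at 20 per arm, 45–54% at 40 per arm, and 29–41% at 20 per arm with the cited PCOS rates. These figures assume two-sided 0.05 and that the quoted rates apply in the subset.

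A stronger reading would give a 19% chance of at least one false positive across the four subsets. Under the plan's small-count rule, read as Fisher when any cell is below 5, the figure is about 7–11%. Roughly 19% applies only with chi-square throughout, and either figure needs all four subsets to reach 20 per arm and to be independent. It would also be too strong to say that an interaction test settles the matter, since its power is about 24–31% even if the whole effect lay in one stratum.

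**What to change.** For each of the four risk factors, fit the logistic model to all randomised women with an outcome, including an arm-by-factor term. Report the effect with its 95% CI in women with and without the factor, and the interaction estimate with its CI. State that no conclusion will be drawn from significance within a subset. Keep 20 per arm only as the minimum for showing an estimate, and present sparse strata descriptively, where the model may be unstable.

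The cost is a few sentences of analysis text; the data, the logistic regression and the software are already planned. The downside is the low power of the interaction test. The plan should say that the interaction is read as an estimate with its CI and that a non-significant result is not proof of equal effects.
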